#### Study procedure (treatment arm): therapeutic plasma exchange (TPE)

The TPE treatment will be initiated within 6 h after randomization. Duration of TPE treatment is approximately 120–180 min. An additional second TPE can be performed at 24 h following randomization if the patient has responded to first treatment as indicated by any reduction of NE dose *and* if NE dose is still ≥ 0.4 µg/kg/min after 24 h. Both unfractionated heparin (UFH) and citrate may be used as anticoagulant medication. To ensure treatment comparability between different patients, we will replace plasma in a fixed ratio of 1.2 × the individual patient’s total plasma fluid. The individual patient’s total plasma fluid will be calculated on each trial site from hematocrit and body weight (BW) following the formula by Kaplan et al. (16). The formula used calculates the estimated plasma volume (ePV) as: *ePV* = *[[0.065* × *BW* [kg]*)]* × *[100-Hematocrit* [%]*]]* × *10* [ml]. To avoid potential allergic reactions, anti-histamines (Clemastin (Tavegil®) 2 mg and Ranitidin (Ranitic®) 50 mg, both given as intra-venous (i.v.) push), will be administered before TPE (and in the control group at time of randomization). No additional cortisone push should be given as anti-allergic prophylaxis immediately before TPE treatment.

### Outcomes

#### Primary endpoint

The primary endpoint is 28-day mortality (Table 1).

**Table 1 Tab1:** Endpoints

PRIMARY Endpoint	28-day mortality
KEY SECONDARY Endpoint	
Extent of organ failure	indicated by: Mean Sequential Organ Failure Assessment (SOFA) score over the first 7 days following randomization and Organ support-free days (total days free of invasive ventilation, vasopressors/inotrops and RRT) until d28
(Further) SECONDARY Endpoints	
90-day mortality	
1-year mortality	
Length of stay (LOS)	Intensive Care Unit (ICU) LOS [days] Hospital LOS [days]
Basic hemodynamics 0 and 12 h, d1–7	Days free of vasopressor until day 28 [days] Norepinephrine dose [µg/kg/min] Dobutamine dose [µg/kg/min] Epinephrine dose [µg/kg/min] Vasopressin dose [U/kg/min] Vasoactive inotropic score (VIS) Mean arterial pressure (MAP) [mmHg] Heart rate (HR) [bpm] Central venous pressure (CVP) [mmHg] Central venous saturation (ScvO_2_) [%]
Extended hemodynamics 0 and 12 h, d1–7	Cardiac index (CI) [l/min/m^2^] Stroke volume variance (SVV) [%] Systemic vascular resistance index (SVRI) [dyn*s*cm-5*m^2^] Global end diastolic volume index (GEDI) [ml/m^2^] Extravascular lung water index (ELWI) [ml/kg] Pulmonary vascular permeability index (PVPI)
Arterial blood gas analysis (BGA) 0 and 12 h, d1–7	pH PCO_2_ [mmHg] HCO_3_^−^ [mmol/L] PO_2_ [mmHg] Lactate [mmol/L]
Respiratory function 0 and 12 h, d1–7	Days free of ventilator until day 28 [days] PO_2_/FiO_2_ ratio (PF ratio) Tidal volume (VT) [ml] Positive end-expiratory pressure (PEEP) [cmH_2_O] Peak pressure (Ppeak) [cmH_2_O] Plateau pressure (Pplat) [cmH_2_O] Respiratory Rate (RR) [1/min] Inspiratory Time (Tinsp) [s] Inspiratory Flow [l/min] End tidal CO_2_ (etCO_2_) [mmHg]
Renal function 0 and 12 h, d1–7, ICU discharge	Days free of renal replacement therapy (RRT) until day 28 [days] Presence of acute kidney injury (AKI) (KDIGO) [yes/no], 0 and 12 h, d1–7, ICU discharge AKI stage (KDIGO) [Stage 1 to 3], 0 and 12 h, d1–7, ICU discharge Need for RRT [yes/no], 0 and 12 h, d1–7, ICU discharge Estimated Creatinine-based Glomerular Filtration Rate (eGFR) (CKD-EPI) [ml/min], 0 and 12 h, d1–7, ICU discharge Fluid intake [ml/d], d1–7 Urine output [ml/d], d1–7 Ultrafiltration [ml/d], d1–7 Net daily fluid balance [ml/d], d1–7
Liver function 0 and 12 h, d1–7, ICU discharge	Bilirubin [µmol/l] Aspartate aminotransferase (AST) [U/l] Alanine aminotransferase (ALT) [U/l] Alkaline phosphatase (AP) [U/l] Gamma-glutamyl transferase (GGT) [U/l] Cholinesterase (CHE) [kU/l] Albumin [g/l]
Sepsis associated coagulopathy 0 and 12 h, d1–7	Differential full blood count (including hemoglobin (Hb) [g/dl], white blood cell count (WBC) [Tsd/µl], polymorphonuclear leucocytes (PMN) [Tsd/µl], lymphocytes [Tsd/µl], monocytes [Tsd/µl], platelets [Tsd/µl], and schistocytes [%]) Fibrinogen [g/l] D-Dimer [mg/l] International normalized ratio (INR) Lactate dehydrogenase (LDH) [U/l] Antithrombin (AT)-III [%] Protein C [%] vWF:Ag [IU/dl] (*only* at 0 and 24 h) ADAMTS13 [%] (*only* at 0 and 24 h) ISTH-DIC Score [0–8 points]
Inflammatory response 0 and 12 h, d1–7	C-reactive protein (CRP) [mg/l] Procalcitonin (PCT) [µg/l] Interleukin-6 (IL-6) [ng/ml] Ferritin [µg/l] Neutrophil/lymphocyte ratio
Cardiac function 0 and 12 h, d1–7, ICU discharge	Creatine kinase (CK) [U/L] Myoglobin [ug/L] NT-proBNP [ng/L] Troponin T, high sensitive [ng/L]
Secondary infections until ICU discharge	Presence [yes/no] Species [gram + /gram − /viral/fungal] Viral reactivation (HSV, EBV, and CMV copies by PCR) (*only* at days 7 and 14)
SAFETY ENDPOINTS	
Bleeding complications until day 7	Vascular access-related Intra cerebral bleeding Others
Bleeding complications until day 7	Acute myocardial infraction Thrombosis/ Embolism
Allergic reactions until day 7	Acute hemodynamic worsening + tachycardia
Infections until day 7	Infections related to the entry site of the dialysis catheter or new bloodstream infections
Transfusion associated lung injury (TRALI) until day 7	Significant worsening of respiratory function + typical X-ray deterioration
Severe thrombocytopenia until day 7	Occurrence of and time to severe thrombocytopenia (< 5000/μl)
Other device related Severe Adverse Events (SAEs) until day 7	Other device related SAEs such as air embolism or clot formation in the vein around the catheter with a risk of dislodgement of the clot to the lung
Other SAEs until day 7	SAEs that are not related to the critical illness / sepsis per se and are classified as possibly, probably or causally provoked by the intervention

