#### Safety endpoints

The following safety endpoints are assessed until day 7 following randomization (Table 1): bleeding complications, thrombotic complications, allergic reactions, infections related to the entry site of the dialysis catheter or new bloodstream infections, transfusion related lung injury, occurrence of, and time to severe thrombocytopenia (< 5.000/μl) and other device related serious adverse events (SAEs). Given the profound severity of disease in the patients under investigation (hospitalized patients under critical care, shock and (multi) organ failure) a variety of AEs and SAEs are expected to incept as part of the natural history of disease and will therefore not be reported. Furthermore, SAEs, that are not directly related to critical illness / sepsis per se and are classified as possibly, probably, or causally provoked by the intervention, will additionally be recorded until day 7. Potential SAEs that are directly related to critical illness will thus not be explicitly reported.

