#### Analyses of safety endpoints

Absolute and relative frequencies of all safety endpoint events will be displayed for the whole population and separately for experimental and control group and will be compared using chi-squared tests.

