## Discussion

To the present time, no adequately powered randomized clinical trial has investigated the effect of TPE on survival in septic shock patients. Previous studies investigating TPE in sepsis have either been underpowered or included a heterogenous study population [7, 8]. Therefore, despite promising data demonstrating more rapid hemodynamic stabilization [10, 14], the role of TPE as a potential adjunctive treatment option in septic shock remains unclear. As we have observed the most obvious clinical effects (during the feasibility trial) in sepsis patients that have been treated very early after onset of shock and that demonstrated particularly profound hemodynamic instability, we have designed the inclusion criteria of the here described study accordingly. This effort to homogenize the participants (early and severe septic shock) stands in contrast to previous trials that have investigated a broader range of septic patients.

TPE using human plasma as replacement fluid has potential adverse effects, including infectious and non-infectious (allergic reaction, transfusion associated lung injury (TRALI), citrate toxicity, hypotension) [16] with pruritus and urticaria most commonly observed [17]. However, severe adverse events are extremely rare [18] and incidence of adverse events requiring discontinuation of treatment lies at around 0.2% [17]. Of note, no adverse events were observed in our previous EXCHANGE feasibility pilot study [10] and the randomized EXCHANGE-1 trial, investigating patients with literally the same characteristics [19]. To avoid potential allergic reactions, anti-histamines will be administered before TPE (and in the control group at time of randomization). Importantly, there is no additional invasive exposure of the patient. The central line used for TPE will be inserted for clinical management (e.g., RRT) only and all biosamples will be drawn via catheters (central venous and arterial), which have been placed independent of biosampling for treatment and monitoring indication. Therefore, no additional puncture of the skin needs to be performed for biosampling.

The investigators convinced that a risk–benefit consideration clearly favors performance of the here proposed clinical trial. Importantly, this is an investigator-initiated trial, funded by the DFG without any competing commercial or financial interests involved.

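### The allergic-reaction safety row is non-specific in septic shock and misses non-serious skin reactions, so it is unlikely to show a modest excess with plasma exchange

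*Protocol article*

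**What the plan says.** In the protocol article, Table 1 has a safety row for allergic reactions until day 7. Its whole content is "Acute hemodynamic worsening + tachycardia". There is no skin or airway sign, no threshold and no link in time to the plasma.

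The Safety endpoints section sets the window ("The following safety endpoints are assessed until day 7 following randomization") and lists "bleeding complications, thrombotic complications, allergic reactions, infections related to the entry site of the dialysis catheter or new bloodstream infections" among other items, without defining allergy further. It adds: "Potential SAEs that are directly related to critical illness will thus not be explicitly reported".

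The Analyses of safety endpoints section says that event frequencies by arm "will be compared using chi-squared tests".

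The Discussion, on adverse effects of TPE with human plasma, reports "pruritus and urticaria most commonly observed".

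**The concern.** The criterion has two separate weaknesses.

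- **Specificity.** The eligibility criteria admit only patients in early septic shock with a high vasopressor requirement. Haemodynamic deterioration with a fast heart rate can come from the disease in either arm on any day of the first week.
- **Sensitivity.** The reactions that the Discussion calls commonest do not meet the row. The remaining catch-all rows in Table 1 accept only serious adverse events, so a non-serious urticarial reaction has no place among the safety endpoints.

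Allergic reaction is a named harm of the plasma exposure and appears in the Abstract as a safety endpoint. If disease events in both arms dominate the count and skin reactions are left out, the trial may report no difference in allergic reactions when there is a modest one.

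**Working it through.** **1. Inputs from the article.** Enrolment is 274 at 1:1, so 137 per arm. The article gives no figure for this endpoint. Its only sample size figure, 131 per group for 60% against 42% mortality, reproduces:

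- Uncorrected n = [1.96·√(2·0.51·0.49) + 0.842·√(0.60·0.40 + 0.42·0.58)]² / 0.18² = 119.9, that is 120.
- Continuity corrected: (119.9/4)·[1 + √(1 + 4/(119.9·0.18))]² = 130.8, that is 131.

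This confirms the planning basis but does not bear on allergy.

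**2. Exposure against window.** The Interventions section gives 120 to 180 minutes per exchange and allows one repeat. Two exchanges take at most 2 × 3 h = 6 h. Seven days are 168 h, and 6/168 = 3.6%. Nearly all of the window lies outside an exchange, though reactions may also begin soon after one.

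**3. Assumptions.** Let b be the proportion in both arms whose septic course meets the row, and e the proportion of TPE patients with a true reaction that meets it. The article gives neither. I take e = 5% and b = 0, 10%, 20% and 30%. The observed rates are then b in controls and b + (1 − b)·e with TPE.

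**4. Power at 137 per arm, two-sided 5%, from exact binomial enumeration.**

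| b | Control | TPE | Uncorrected chi-squared | Continuity corrected | Share of counted TPE-arm events caused only by TPE |
|---|---|---|---|---|---|
| 0 | 0% | 5.0% | 92% | 69% | 100% |
| 10% | 10% | 14.5% | 20% | 16% | 31% |
| 20% | 20% | 24.0% | 13% | 10% | 17% |
| 30% | 30% | 33.5% | 9% | 7% | 10% |

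The last column is (1 − b)·e divided by the TPE rate, for example 0.045/0.145 = 31%.

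Check of the 10% row by normal approximation: z = [0.045 − 1.96·√(2·0.1225·0.8775/137)] / √[(0.145·0.855 + 0.10·0.90)/137] = −0.826, which gives 20%.

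Check of the zero-background row: 4 events against 0 gives p = 0.044 uncorrected but 0.13 corrected, and 6 against 0 are needed for the corrected test (p = 0.039). With 137 patients at 5%, the chance of at least 4 events is 92% and of at least 6 is 69%.

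**5. Smaller excess.** At e = 2% with no background, power is about 29% uncorrected and 6% corrected. With b = 10% it is about 8% uncorrected. Rarity alone would leave an excess of this size hard to show.

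**6. Skin-only reactions.** A reaction with only pruritus or urticaria contributes zero to the count, whatever its true rate.

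**The case against.** A reader might infer that the endpoint cannot show a TPE reaction at all. The document does not support that. A severe reaction with hypotension and tachycardia meets the row, the randomised controls supply the background rate so that a large excess could appear, and serious reactions attributed to the intervention enter the row for other SAEs.

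A reader might also infer a rule that every septic deterioration counts as allergy. The row is headed allergic reactions, and the Safety endpoints section says that events belonging to the disease course will not be reported. That shows an intent to keep them out. It does not say how an investigator is to tell the two apart when the only criteria are signs they share, so the specificity point stands with less force than a literal reading would give it.

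It can further be said that omitting mild skin reactions is a choice of scope. Both arms receive antihistamines, many patients may be unable to report itching, and the Discussion summarises outside experience in which severe events are rare and "incidence of adverse events requiring discontinuation of treatment lies at around 0.2" percent. This is fair for pruritus. It is weaker for urticaria, which can be seen, and the article does not state that only severe reactions are meant.

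The power figures rest on assumed rates, and the 92% benchmark flatters the specific definition because an uncorrected chi-squared test is used with very few events. Both criticisms are accepted, which is why the corrected column is shown.

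Finally, the article condenses a full protocol that may hold a fuller definition. But the article does state a criterion here, and that criterion fits poorly with its own Discussion.

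**Conclusion.** The point holds in a limited form. The stated criterion is non-specific in this population, misses non-serious skin reactions entirely, and is unlikely to show a modest excess with TPE. Severe reactions are not lost.

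On the assumed rates, a background of 10% to 30% cuts power for a 5% excess from about 92% to between 20% and 9% uncorrected, or from about 69% to between 16% and 7% corrected. These figures assume the same background in both arms, that investigators count disease-related worsening, and that every true reaction meets the row. They show direction and rough size and are not estimates for this trial. Zero background is a best case that a better definition would approach but need not reach.

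The primary and key secondary analyses are unaffected. The change is worth making because the harm is specific to the plasma exposure and the remedy is cheap.

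**What to change.** Reconcile the Table 1 row with the Discussion:

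1. Redefine the row so that an event needs at least one allergic sign, including observable skin signs such as urticaria. Record it identically in both arms to day 7 and keep the between-arm comparison in Analyses of safety endpoints.
2. Record the timing of each event relative to any plasma exchange. Report exchange-related reactions, including haemodynamic worsening attributed to the plasma, descriptively in the TPE arm. Timing should not be part of the compared definition: controls have no exchange, so their count would be zero by construction and the chi-squared test would mean nothing.
3. Keep haemodynamic worsening plus tachycardia as a separate descriptive item in both arms.

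The cost is one reworded row and one or two eCRF fields. The downside is some judgement on attribution by unblinded staff. It is confined mainly to the descriptive items, and objective signs and recorded times limit it. No treatment or clinical rule changes.

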### Blinding

The clinical team responsible for the participant (physicians, nurses, and others) involved with direct patient care will not be blinded to allocation group due to the inherent difficulty in blinding the intervention. Measures will be taken to ensure that the information about allocation will not disseminate beyond the immediate group of caregivers responsible for patient care. The intensive care physician will not be allowed to share any information regarding the allocation group. Patients, their legal representatives, and family will only be informed that the patient has been randomized into the study. Health personnel responsible for outcome assessment at follow-up will be blinded to the allocation of the intervention when possible.

The author group, trial statistician, and the trial coordinating team will be blinded to group allocation. In order to enable an unbiased assessment of the intervention and manuscript writing process, the two study arms will be coded as “X” and “Y”. Two manuscripts will be drafted one assuming that “X” corresponds to the TPE group and “Y” to the control group—and one draft assuming the contrary. The code will be broken upon acceptance of both drafts by the author group.

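### The 'Allergic reactions' safety row rests on hemodynamic signs that cannot separate allergy from shock, and it leaves out the skin reactions the protocol calls most common.

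*Protocol article*

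**What the plan says.** In Table 1 (Outcomes), the row for allergic reactions until day 7 has one entry: "Acute hemodynamic worsening + tachycardia". The Safety endpoints section names allergic reactions, refers to Table 1 and adds no criterion.

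The same section limits what else is reported. It states that "Potential SAEs that are directly related to critical illness will thus not be explicitly reported". The residual category takes serious adverse events not directly related to critical illness and "classified as possibly, probably, or causally provoked by the intervention".

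Under Analyses of safety endpoints, event frequencies are shown "separately for experimental and control group and will be compared using chi-squared tests".

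The Discussion describes the adverse effects of TPE with human plasma, "with pruritus and urticaria most commonly observed". It lists hypotension as an adverse effect distinct from allergic reaction.

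On exposure, the treatment-arm section says "Duration of TPE treatment is approximately 120–180 min" and "An additional second TPE can be performed at 24 h following randomization". Under Blinding, the treating team "will not be blinded to allocation group due to the inherent difficulty in blinding the intervention".

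**The concern.** A safety row labelled as allergy should capture allergic reactions and little else. This one is fixed on two signs that are part of the disease being treated. Eligibility requires norepinephrine of at least 0.4 μg/kg/min, or at least 0.3 μg/kg/min plus vasopressin, despite fluid resuscitation. A further fall in pressure with a fast heart rate during the following week needs no allergic cause in such a patient.

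The row also has no place for the reactions the authors themselves describe as most frequent with this treatment.

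At stake is how the safety result is read. A difference between arms could reflect allergy, procedural hypotension or the course of shock, and these call for different preventive measures. No difference could be taken as reassurance about a plasma-based therapy that the authors say could change standard of care.

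**Working it through.** The plan states no figure for this endpoint, so there is none to reproduce. The check compares the relevant sections.

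**1. Is the cell a criterion or only a label?** The TRALI row has the same form: two findings joined by a plus sign, one respiratory and one radiological. Read alongside it, the allergy cell works as a criterion. Other rows in that column list categories or examples, so the form alone does not settle the matter. Both readings are followed below.

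**2. Reading A: the cell is the criterion.**
- Population: every patient is in early refractory shock (Eligibility criteria), so the signs can arise from the disease in either arm.
- Exposure: a session lasts two to three hours, with an optional second at 24 h. The row runs to day 7 and states no link to plasma or TPE exposure.
- Filter: the Safety endpoints section sets aside natural-history events. Applying that rule here means deciding whether a given deterioration is sepsis or allergy. No criterion for the decision is stated, and those at the bedside know the allocation.

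A simple expression shows the effect of events that pass the filter. Let *a* be the true allergy risk under TPE (zero in control), *b* the risk of shock-related events counted in either arm, and *h* the risk of procedural hypotension counted under TPE. Treat them as independent, with *b* equal between arms.

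- Control: *b*
- TPE: 1 − (1 − *a*)(1 − *b*)(1 − *h*)
- Difference with *h* = 0: [1 − (1 − *a*)(1 − *b*)] − *b* = *a*(1 − *b*), smaller than *a*
- Difference with *a* = 0: *h*(1 − *b*), an apparent allergy excess where there is none

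Shared shock events therefore shrink a true excess, while procedural hypotension creates or enlarges one. The net direction is not fixed. The document gives no value for *a*, *b* or *h* under this definition, so no size is computed.

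**3. Reading B: the cell marks when a diagnosed allergy counts.** The row then measures allergy, but only the hemodynamically relevant kind. Pruritus and urticaria alone do not meet it. The residual category takes serious events only, so a non-serious skin reaction fits no listed safety endpoint.

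**4. Result.** Reading A lacks specificity. Reading B omits the most common form of reaction. The article does not say which applies.

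**The case against.** The strongest reply is that the row label cannot be dropped. The endpoint is allergic reactions, the cell is a few words, and the section rule on natural-history events governs the table. A reader might infer that every progression of shock in either arm would be counted as allergy. The documents do not support that: the label and the rule make it doubtful. What remains is that the sorting depends on unblinded judgement without a criterion.

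A reader might also infer that the row does not measure allergy at all. On Reading B that is wrong, because it measures severe allergy. Restricting to consequential reactions is defensible in patients this ill. Both arms receive two intravenous antihistamines, pruritus is hard to elicit under sedation, and the Discussion reports severe events as extremely rare, discontinuation at around 0.2%, and no adverse events in the two earlier studies. If severe-only is the intention, it should be stated.

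Third, this is a condensed article, and the full protocol or eCRF may contain fuller criteria. So it cannot be said that skin reactions are recorded nowhere, only that they fall outside the listed safety endpoints when not serious. Nor is hypotension unrecorded: Table 1 collects MAP, heart rate and vasopressor doses at 0 and 12 h and on days 1 to 7. The point stands because the article states a criterion, and that criterion is poorly chosen.

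Finally, the contrast between a short session and a seven-day window might suggest that most counted events would be misclassified. Time outside a session is not an error rate and is not used as one here.

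**Conclusion.** The point holds as a definition that is stated but badly fixed. On one reading the criterion cannot separate allergy from shock progression or procedural hypotension except by unblinded judgement. On the other it covers severe allergy only and leaves out pruritus and urticaria. Either way the between-arm test is hard to interpret as a comparison of allergic reactions.

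No event rate or size of error can be given from the document. The conclusion rests on the article's own wording and assumes that no fuller definition in an unseen document overrides Table 1. The primary mortality conclusion is unaffected, so this is a low-cost improvement to consider rather than a threat to the trial.

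**What to change.** Redefine the row as either of the following, occurring within a fixed time after plasma or TPE exposure that the investigators set in advance:

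- urticaria or other visible allergic skin signs, with pruritus where it can be elicited;
- anaphylaxis with hemodynamic worsening not explained by sepsis.

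Report hemodynamically relevant and skin-only reactions separately, so that the severe category the authors may have intended stays visible. Optionally, report hypotension during TPE as its own descriptive item for the TPE arm only.

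The cost is a small amendment to the eCRF and Table 1, a favorable ethics opinion before use (Amendments), and roll-out to about 26 centers. No extra procedure is needed on patients. The change does not remove all subjectivity: whether a deterioration is explained by sepsis still has to be judged by unblinded staff, and pruritus will be under-recorded in sedated patients. Urticaria, which is visible, and the exposure window reduce the reliance on that judgement.

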### Statistical methods

#### Analyses populations

The intention-to-treat (ITT) population comprises all randomized patients. Patients will be analyzed as randomized independently of the performed intervention. Primary analyses of all efficacy endpoints will be conducted on the ITT population.

The per-protocol (PP) population comprises all patients that received the randomized intervention and were complying with the study protocol until the end of the follow-up period. Supplementary efficacy analyses will be conducted on the PP population.

The safety population comprises all patients that received the study intervention. Patients will be analyzed as treated. Analyses of safety endpoints will be conducted on the safety population.

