#### Analyses of secondary endpoints

Analyses of the key secondary endpoints will be performed as follows:(i)The mean SOFA score will be analyzed as degree of organ failure measured by the per-patient mean daily SOFA score over 7 days. In case a patient dies before day 7, the daily SOFA score will be registered as 24 points for the following days until day 7. A linear regression model will be used for comparing the treatment arms, which includes mean daily SOFA score over 7 days as dependent variable, and treatment group, sex, pulmonary focus of infection (yes/no), baseline lactate (< 4.5/ ≥ 4.5 mmol/l), and center as independent variables. Superiority of the experimental intervention compared to the control intervention can be concluded if the upper boundary of the two-sided 95% confidence interval for the adjusted mean difference (experimental intervention minus control intervention) is below 0.A sensitivity analysis for the SOFA score will be performed using an exact test based on trimmed means [15]. This method follows the ITT principle in taking all randomized patients into account in the analysis without hypothesizing SOFA values for patients who die before day 7.(ii)Organ support-free days until day 28, determined as total days without need for invasive ventilation, vasopressor/inotropes, and RRT until day 28, will be analyzed similarly with a linear regression model with stratification factors of the randomization as co-variates. In case a patient dies before day 28, each remaining day until day 28 will be counted as a day with organ failure.

The confirmatory assessment of key secondary endpoints will be done in the above specified order as soon as the primary analysis of the primary endpoint is significant.

Other secondary endpoints:

The 90-day mortality (dead at day 90: yes or no) will be analyzed in line with the primary analysis of 28-day mortality. In addition, 28-/90-day mortality will be analyzed as time-to-event endpoint. The survival curves until day 28/90 will be estimated using the Kaplan–Meier method and compared using the log-rank test. Additionally, a Cox regression model will be utilized to estimate the hazard ratio between the treatment arms.

Other secondary endpoints (e.g., ICU length of stay, hospital length of stay, hemodynamics, arterial blood gas analysis) will be summarized by treatment group and compared with appropriate statistical tests.

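### The only platelet event in the safety analysis is a count below 5000/µl, a cut-off given without rationale, so a null result on it would say little about TPE and platelets

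*Protocol article*

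**What the plan says.** The safety block of Table 1 lists "Occurrence of and time to severe thrombocytopenia (< 5000/μl") until day 7. The Safety endpoints section gives the same definition: "occurrence of, and time to severe thrombocytopenia (< 5.000/μl) and other device related serious adverse events (SAEs"). The point in 5.000 is the German thousands separator, so the two places agree. Neither explains the cut-off, and no second band or relative fall is defined.

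The section Analyses of safety endpoints starts with tabulation: "Absolute and relative frequencies of all safety endpoint events will be displayed for the whole population and separately for experimental and control group". It then names the test: these frequencies "will be compared using chi-squared tests". The set analysed is as treated: "The safety population comprises all patients that received the study intervention".

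Platelets also appear elsewhere. In Table 1, under sepsis-associated coagulopathy, at 0 and 12 h and on days 1 to 7, the list opens with "Differential full blood count (including hemoglobin (Hb") and includes the platelet count. Analyses of secondary endpoints states that the other secondary endpoints "will be summarized by treatment group and compared with appropriate statistical tests".

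**The concern.** The endpoint reduces a week of platelet counts to one yes/no event at a single extreme value. A patient who falls from a normal count to 6000/µl is recorded as having no event. If counts below 5000/µl are rare, both arms will show few or none, and the row will look reassuring whether or not TPE lowers platelets.

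This matters because the trial is open-label and the intervention is extracorporeal, with heparin or citrate anticoagulation. A laboratory threshold is one of the few safety measures that does not depend on an unblinded clinician's judgement. The adverse-event route is narrow: the Safety endpoints section leaves out serious events tied directly to critical illness and keeps those judged possibly, probably or causally due to the intervention. Platelet falls are grouped in Table 1 with septic coagulopathy, so a fall that stays above 5000/µl could be put down to sepsis and not reported.

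**Working it through.** **Inputs from the article.** 137 patients per arm (Abstract, Methods); event defined as platelets below 5000/µl by day 7 (Table 1; Safety endpoints); chi-squared comparison (Analyses of safety endpoints). The safety set may be slightly smaller than 137 per arm.

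**Input not in the article.** The rate of counts below 5000/µl. I assume 0.1% to 2% in controls and show the range.

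**The plan's own figure.** It states no figure for this endpoint; the sample size sets the number of patients available. For 60% versus 42%, two-sided 5%, 80% power, the usual two-proportion formula gives 120 per group, and 131 with the continuity correction, as stated. Allowing 5% drop-out, 262 / 0.95 = 275.8, close to the stated 274 (137 per arm).

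**Power of the safety comparison.** Expected control events = 137 × p. Chance of no event in the whole trial if both arms share p = (1 − p)^274. Power comes from enumerating two binomials with n = 137 and counting outcomes where the uncorrected two-sided 5% chi-squared test rejects in the direction of harm.

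| Assumed control rate | Expected control events | No event in either arm | Power, doubling | Power, tripling |
|---|---|---|---|---|
| 0.1% | 0.14 | 76% | 0.0% | 0.1% |
| 0.25% | 0.34 | 50% | 0.4% | 1.4% |
| 0.5% | 0.69 | 25% | 2.5% | 7.8% |
| 1% | 1.4 | 6% | 8.2% | 20% |
| 2% | 2.7 | 0.4% | 14% | 39% |

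**Smallest split that reaches p < 0.05 with no control events.** Chi-squared = (k/137)² / [p̄(1 − p̄)(2/137)], with p̄ = k/274.
- k = 3: p̄ = 0.01095; 0.000480 / 0.000158 = 3.03; p = 0.082.
- k = 4: p̄ = 0.01460; 0.000852 / 0.000210 = 4.06; p = 0.044.

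The uncorrected test is the favourable case. With a continuity correction, 4 versus 0 gives 274 × (4 × 137 − 137)² / (137² × 4 × 270) = 2.28, p = 0.13.

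**Two further markers.** For a 95% chance of even one event in an arm, the true rate must be 1 − 0.05^(1/137) = 2.2%. For an expected count of 5 per arm, a common minimum for a chi-squared test, it must be 5/137 = 3.6%.

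**Same doubling at a commoner definition.** If a band is met by 10% or 20% of controls (assumed), power is 65% or 96%.

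**The case against.** The strongest reply is that platelets are followed elsewhere. The counts at 0 and 12 h and on days 1 to 7 are a listed secondary variable, to be compared between arms, and bleeding is a separate safety endpoint. An extreme sentinel event alongside a continuous secondary variable is a defensible design, and no safety endpoint here is powered. This stands in part: a reader might infer that the trial cannot detect platelet loss caused by TPE, and the article does not support that. What remains is that the secondary comparison has no fixed method and sits among many laboratory values, and that the safety analysis takes only the one extreme cut-off from these counts.

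Three other stronger readings also fail:
- That the endpoint itself can show nothing. It is very insensitive, but 4 versus 0 would reach p = 0.044.
- That such counts will almost never be recorded. The article gives no frequency; rarity is an assumption, and the power figures depend on it.
- That 5000 is a typing error. Both places agree, and nothing in the article shows that another value was meant.

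**Conclusion.** The point holds as a weakness in how one safety endpoint is fixed; there is no contradiction in the article. That falls staying above 5000/µl are non-events follows from the definition alone. The size rests on the assumed control rate of 0.1% to 2%: at most about three control events expected, at most about 14% power for a doubling and 39% for a tripling. Within that range, a null result on this row would not be evidence that TPE leaves platelets unaffected. If such counts were clearly commoner than 2%, the criticism would weaken. The primary endpoint is untouched.

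**What to change.** Confirm whether 5000/µl is intended and, if so, state why. In either case, add to the safety analysis, by arm and from counts already collected:
- the platelet nadir and the maximum fall from baseline by day 7;
- occurrence of at least one less extreme band, chosen and fixed by the sponsor before the data are seen;
- if time to that event is analysed, death before day 7 as a competing event, since the plan assumes 60% control mortality by day 28.

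Keep the count below 5000/µl as a descriptive row, and show the planned secondary platelet comparison beside it. The cost is wording and programming; no new sampling is needed. The drawback is that more events will be tabulated, many of them due to sepsis, but they are compared between arms.
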